# LIST OF ABBREVIATIONS

ANSM Agence nationale de sécurité du médicament et des produits de santé
(National Agency for the Safety of Medicines and Health Products, equivalent to the FDA)

BESS Balance Error Scoring System

CNIL Commission nationale de l’informatique et des libertés (French Data Protection Authority)

CRF Case report form

CV Curriculum vitae

DPO Data Protection Officer

EPMS Entrainement physique militaire et sportif (Military and sports physical training)

GCP Good clinical practice

IRB Institutional Review Board (Comité de Protection des Personnes)

IRBA Army Biomedical Research Institute (Institut de recherche biomédicale des armées)

RM Reference methodology

RPPS Shared directory of healthcare professionals (Répertoire partagé des professionnels de santé)

SSA Service de santé des armées (Armed Forces Health Service)

STAC Stage de sélection des commandos marines (Marine commando selection course)

POT Potential optimization techniques

# RESEARCH SUMMARY

| Sponsor | Direction Centrale du Service de Santé des Armées |
| --- | --- |
| Person who will direct and supervise the study | [name]  Unité neurophysiologie du stress, Département neurosciences et sciences cognitives, Institut de Recherche Biomédicale des Armées, [name] |
| Title | Preventing injury in the military by optimizing body awareness - POSITION |
| Justification / context | Physical activity and sport play an important role in the military environment, and help to develop and optimize the operational capacity of combatants. Nevertheless, the injury rate is high, and the identification of risk factors that are amenable to primary prevention measures is a key challenge in the context of maintaining combatants in good health. Military epidemiological data show that the majority of injuries are acute trauma due to a fall following a loss of balance. These data suggest that postural balance may moderate the occurrence of injuries that occur during physical activities in this context. Furthermore, the high stress levels that individuals are exposed to during their military physical activities could contribute to a degradation in postural balance. The POSITION project investigates the cognitive mechanisms involved in postural awareness as a risk factor for injury, and as a target for a primary prevention strategy based on Potential Optimization Techniques (POTs)^[[1]](#footnote-1)^. POTs could improve postural control, and reduce the intensity of the psychobiological stress response, thereby reducing the rate of fall-related injuries that occur during physical activities in the military context. |
| Objectives | The main objective is to evaluate the effectiveness of POTs in preventing fall injuries during physical activities in the military context.  Secondary objectives:  The first secondary objective is to test the mechanistic hypothesis that POTs can reduce the risk of fall injury by improving postural awareness.  The second secondary objective is to test the mechanistic hypothesis that POTs can reduce the risk of fall injury by decreasing the intensity of the psychobiological stress response during physical activities in the military context.  The third secondary objective is to use machine learning to develop a predictive model of the risk of fall injury, based on clinical (the BESS test) and paraclinical (posturography) measurements taken prior to the start of physical activities in the military context.  The fourth secondary objective is to evaluate the persistence over time of the effectiveness of a POT intervention in preventing the risk of fall-related injury. The rate of fall injuries will be compared for POTs and active control groups among participants who continue to engage in physical activities after the end-of-study visit (and complete the selection course). |
| Research outline | This is an open, prospective, controlled, single-center cohort study. |
| Evaluation criteria | The primary endpoint is the rate of fall-related injuries due to a loss of balance in each of the two groups (POTs *vs*. active control).  Secondary endpoints:  The first secondary objective comprises two evaluation criteria: 1) self-reported scores on the Postural Awareness Scale pre- and post-intervention, and at the start of each session; 2) variation in measures of postural balance pre- and post-intervention.  The second objective also comprises two criteria: 1) self-reported scores on Cohen’s Perceived Stress questionnaire pre- and post-intervention, and at the start of each session; 2) variation in measures of allostatic load in saliva pre- and post-intervention (corticotropic axis: cortisol, DHEA, oxidative stress; the autonomic nervous system: alpha amylase and chromogranin A).  The evaluation criterion for the third secondary objective will be the correct prediction of the risk of fall injury by the machine learning model.  The evaluation criterion for the fourth secondary objective will be the rate of fall-related injuries following a loss of balance in each of the two groups (POTs *vs*. active control), between the end of the study and the end of the selection course. |
| Inclusion criteria | Informed written consent to participate in the study  Candidate for the selection course  Male or female, over 18 years of age  Eligible for benefits under the French Social Security scheme |
| Exclusion criteria | Participants who have already completed an ‘advanced’ POTs training program (> 10 hours)  Refusal to participate  Person covered by articles L1121-5 to L1121-8 of the French public health code, as follows:   - A pregnant, parturient or nursing woman, - A person detained following a judicial or administrative decision, - Persons who are subject to psychiatric monitoring under articles L3112-1 and L3113-1, and who are not covered by the provisions of article L1121-8, - Adults made a ward of court, or who are unable to give their consent. |
| Schedule | The study will consist of the following visits:   - 1 inclusion visit: inclusion interview and written consent - 1 initial assessment visit: self-report questionnaires (medico-biographical, postural awareness (Postural Awareness Scale) and stress (Cohen’s Perceived Stress Scale), clinical and paraclinical posture measurements and saliva collection. - 4 follow-up visits carried out at the start of the POT or active control sessions, consisting of: self-report questionnaires (postural awareness and perceived stress), - there will be 1 additional visit for participants who suffer a fall-related trauma during the course. The participant will complete questionnaires measuring postural awareness and perceived stress, and a posturography measurement will be performed. - 1 end-of-study visit will take place on the day following the last session of the POT or the active control, or on the day of the fall injury if it occurs before the end of the POT or active control intervention. This visit will include: paraclinical measurement of posture, self-report questionnaires (postural awareness and perceived stress) and saliva collection. |
| Number of subjects | The sample should include 200 participants in each of the two groups (POT and active control), making a total of 400 participants. |
| Statistical analysis | For the primary objective, the effect of the intervention (POT *vs.* active control) on the rate of fall-related injuries will be evaluated using a comparative survival analysis (the Cox model, with clinical variables as potential confounders).  For the first secondary objective, the effect of the POT intervention on postural awareness will be evaluated by comparing the following for the POT group: (*i*) scores on the Postural Awareness Scale at the six measurement times (repeated measures ANOVA), and (*ii*) posturography measurements pre- and post-intervention (paired samples comparison of means).  For the second secondary objective, the effect of the POT intervention on the psychobiological stress response will be evaluated by comparing the following measures for the POT group at six measurement times: (*i*) scores on Cohen’s Perceived Stress Questionnaire (repeated measures ANOVA), and (*ii*) biological stress variables (paired samples comparison of means).  For the third secondary objective, machine learning will be used to evaluate the accuracy of the predictive model of the risk of fall injury based on the accuracy on the prediction.  For the fourth secondary objective, the long-term effectiveness of the POT intervention in preventing fall-related injuries, between the end of the study and the end of the selection course will be evaluated using a comparative survival analysis (the Cox model). |
| Study duration | Duration of inclusion: 24 months  Duration of the intervention: 3 weeks  Duration of each participant’s participation: 4 weeks  Total study time: 25 months |

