## Secondary objectives

The study has 4 secondary objectives:

1. The first is to test the mechanistic hypothesis that POTs reduce the risk of fall-related injury by improving postural awareness.
2. The second is to test the mechanistic hypothesis that POTs reduce the risk of fall injury by decreasing the intensity of the psychobiological stress response during physical activities in the military context.
3. The third is to use machine learning techniques to develop a predictive model of the risk of fall injury, based on a clinical test (BESS) and paraclinical (posturography) measurements taken before physical activities begin.
4. The fourth is to evaluate the persistence over time of the effectiveness of a POT intervention in reducing the risk of fall injury. The assessment will be based on participants who continue to engage in physical activities after the end-of-study visit (and who complete the selection course); the analysis will compare the rate of fall injuries for POTs and active control groups.

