### Follow-up visits

A follow-up visit will be carried out just before each session of the POTs and active control interventions (the schedule for which is shown in Figure 4). During the follow-up visit, the participant will complete self-report questionnaires measuring postural awareness (the Postural Awareness Scale) and perceived stress (Cohen’s Perceived Stress).

Participants who suffer a fall trauma during the course will attend an additional follow-up visit, which will take place on the day of the injury. The military medic, or one of his or her assistants, will collect medical information relating to the trauma, and carry out a posturography measurement. The participant will then complete questionnaires measuring postural awareness (the Postural Awareness Scale) and perceived stress (Cohen’s Perceived Stress).

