### End-of-study visit

Participant follow-up will end either: (*i*) on the day following the last session of the POTs or the active control intervention; or (*ii*) the day they leave the course (for whatever reason), if this occurs before the end of the intervention (POTs or active control).

A posturography measurement will be performed by the military medic, or one of his or her assistants, and the participant will complete questionnaires measuring postural awareness (the Postural Awareness Scale) and perceived stress (Cohen’s Perceived Stress). Finally, a 4 ml saliva sample will be collected.

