## End of the study

### Discontinuation criteria for a participant

Participation will end:

- After the last session of the intervention (POTs or active control),
- On leaving the course (for whatever reason) if this occurs before the end of the intervention.

It will not be possible for a participant who leaves to re-join the program at a later date.

There are no exclusion criteria in the protocol.

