# BIOLOGICAL SAMPLE COLLECTION

Within the framework of the study, we will create a biological collection to meet the stated research objectives, and to be able to carry out other analyses or assays in the light of new facts brought to light by the literature, while the purpose of the study will remain unchanged. Analyses carried out for research purposes will not be used for diagnostic purposes.

The saliva samples that are collected (2 x 2 ml bottles) during inclusion and end-of-study visits will be stored on site at −20°C and then transported under optimal temperature conditions by the investigating team to be stored in the −80°C freezers at IRBA (in a dedicated room, [name]) until they are analyzed.

This will result in a collection of 1,600 samples (2 bottles, 2 measurement times, 400 subjects).

The study’s principal investigator is responsible for saliva sampling.

Each sample will be identified by a code (affixed to cryogenic labels) as follows:

- Subject code: Unit code + Subject number

- Visit number: inclusion visit: Vin; for follow-up visits: V1, V2, V3 and V4; final visit: Vfin. Additional visits will be identified by the code Vadd1, Vadd2, etc., depending on the number of additional visits carried out.

The collection of biological samples undertaken in the context of this study has been declared to the competent authority. After the study has ended, the conservation of the collection of biological samples will be declared to the minister in charge of research and to the director of the Agence Régionale d’Hospitalisation (and submitted to the Institutional Review Board for an opinion if the purpose of the study changes).

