**Analysis of secondary objectives**

For the first secondary objective, the effect of the POTs intervention on postural awareness will be evaluated by comparing the following for the POTs group: (*i*) scores on the Postural Awareness Scale at the six measurement times (repeated measures ANOVA), and (*ii*) posturography measurements pre- and post-intervention (paired samples comparison of means).

For the second secondary objective, the effect of the POTs intervention on the psychobiological stress response will be evaluated by comparing the following measures for the POTs group at all six measurement times: (*i*) scores on Cohen’s Perceived Stress Questionnaire (repeated measures ANOVA), and (*ii*) biological stress variables (paired samples comparison of means).

For the third secondary objective, machine learning will be used to evaluate the accuracy of the predictive model of the risk of fall injury using the following calculation:

|  | $\text{Accuracy=}\frac{\text{True }\text{Fall-related injury }\text{participants + True }\text{Non-fall }\text{participants}}{\text{Total number of participants}}$ |  |
| --- | --- | --- |

where N_prediction of trauma_ is the number of participants for whom the machine learning model predicts the occurrence of a fall injury and who do, in fact, suffer a fall injury during the selection course; N_prediction of_ _good health_ is the number of participants for whom the model predicts the non-occurrence of a fall injury and who do not, in fact, suffer a fall injury during the selection course; and N_total_ is the total number of participants included in the study.

For the fourth secondary objective, the long-term effectiveness of the POTs intervention in preventing fall injuries between the end of the study and the end of the selection course will be evaluated using a comparative survival analysis (the Cox model). Survival curves for POTs and active control groups will be compared using the log-rank test.

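### The end-of-study visit has two incompatible dates, so the objective 4 (persistence) comparison has no fixed start and may begin while sessions are still running

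*Protocol*

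**What the plan says.** **Date of the end-of-study visit.** The Schedule row of the Research Summary gives two alternatives: the day after the last session, "or on the day of the fall injury if it occurs before the end of the POT or active control intervention". The same row also lists a separate additional visit for anyone with a fall trauma, so it assigns two visits to one injury.

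The body gives another rule. Under Follow-up visits, participants with a fall trauma "will attend an additional follow-up visit, which will take place on the day of the injury". Under End-of-study visit, follow-up ends on the day after the last session or "the day they leave the course (for whatever reason), if this occurs before the end of the intervention (POTs or active control"). Discontinuation criteria for a participant agrees: participation ends after the last session or "On leaving the course (for whatever reason) if this occurs before the end of the intervention". Neither of these two sections names injury, by itself, as a trigger.

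**Objective 4.** The Research Summary defines the comparison "among participants who continue to engage in physical activities after the end-of-study visit". Secondary objectives repeats this with its full limit: "participants who continue to engage in physical activities after the end-of-study visit (and who complete the selection course"). Under Analysis of secondary objectives, effectiveness "between the end of the study and the end of the selection course will be evaluated using a comparative survival analysis (the Cox model"), with a log-rank test. No section gives the window a common starting day.

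**More than one additional visit.** Biological Sample Collection states: "Additional visits will be identified by the code Vadd1, Vadd2, etc., depending on the number of additional visits carried out".

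**The concern.** A persistence comparison should contain only time after the programme. If the end-of-study visit falls on the day of an in-programme injury, a participant injured on day 5 who stays is at risk for objective 4 from day 5. A second fall on day 12 would then be a persistence event although sessions run to the end of week three.

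By the plan's own rates, more control than POTs participants are injured during the programme. The control group would therefore supply more early entrants and, if the programme works while it runs, more in-programme second falls. In a simple model this moves the hazard ratio below 1 with no lasting effect. Objective 4 is the plan's analysis of lasting benefit, so its start should not depend on which section is followed.

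**Working it through.** **1. The two rules side by side**, for a participant injured before the last session:

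| | Research Summary, Schedule | Follow-up visits, End-of-study visit, Discontinuation criteria |
|---|---|---|
| Visit on the day of injury | additional visit and end-of-study visit | additional visit only |
| Injured, stays and completes: objective 4 starts | day of injury | day after the last session |
| Injured, leaves the course | does not enter | does not enter |

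The rules differ only for those who are injured, stay and complete the course. For them, only the summary rule puts programme time into objective 4.

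**2. Inputs from the plan** (Calculating the number of subjects required): 50% control, 35% POTs, two-sided 0.05, power 0.80, 10% drop-out, 200 per group. The stated size reproduces approximately. The two-proportion formula with continuity correction gives 183 per group; 183/0.9 rounds up to 204, and 183 × 1.1 rounds up to 202. Without the correction it gives 170 and 170/0.9, or 189. The programme lasts three weeks.

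**3. Hazards**, assumed constant:
- control: ln 2 / 3 = 0.231 per week
- POTs: −ln(0.65) / 3 = 0.144 per week
- implied in-programme hazard ratio: ln(0.65)/ln(0.50) = 0.62

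**4. Second falls inside the programme.** With re-injury hazard equal to first-injury hazard and m = 3 × hazard, the probability of two or more falls in three weeks is 1 − e^(−m)(1 + m).
- control, m = 0.693: 1 − 0.50 × 1.693 = 0.153
- POTs, m = 0.431: 1 − 0.65 × 1.431 = 0.070

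Let f be the share of injured participants who stay; the protocol does not give it. Per 200 per group this means about 30.7f control and 14.0f POTs second falls: 9.2 and 4.2 at f = 30%, and 15.3 and 7.0 at f = 50%. With 180 per group after drop-out, f = 50% gives about 14 and 6.

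**5. Apparent objective 4 hazard ratio when the true later ratio is 1.** This was simulated with 400,000 per group. After the programme both groups have the control hazard, and the course runs 1, 3 or 6 further weeks (an assumption). Summary rule:

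| f | 1 week | 3 weeks | 6 weeks |
|---|---|---|---|
| 10% | 0.975 | 0.986 | 0.990 |
| 30% | 0.930 | 0.965 | 0.980 |
| 50% | 0.906 | 0.959 | 0.967 |
| 100% | 0.859 | 0.928 | 0.948 |

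At f = 50%, in-programme falls are 27%, 13% and 9% of objective 4 events. Under the body rule every setting gives 0.99 to 1.01, which is 1 within simulation error. The limit to course completers was not applied to later injuries.

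**6. If risk varies between participants.** With gamma frailty (variance 0.5 to 1, an assumption), no true later effect and no extra re-injury risk, the summary rule gives 0.96 to 1.07 at f = 25% and 0.89 to 1.01 at f = 50%. The direction is then not fixed.

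**The case against.** The strongest reply is that the body is more detailed than the summary, three of its sections agree, and under them the problem disappears. That is correct, and it is why the firm finding is the contradiction and not a bias that must occur. It does not settle the matter: the summary rule is explicit, and a separate statistical analysis plan that follows the protocol would inherit both dates.

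Second, few injured participants may stay. Objective 4 is limited to those who complete the course, and the background section reports medical unfitness as the leading cause of failure (70%) on a related selection course. This stands. The numbered additional-visit codes suggest that follow-up can continue after an injury, but they are a sample-labelling convention. They fit the body rule better than the summary rule and say nothing about how many stay.

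Three stronger readings are tempting but unsupported:
- *The programme effect is counted twice.* Under the summary rule the first injury coincides with the visit and is not recounted. Only later programme time and second falls could enter.
- *The trial would often declare lasting protection that does not exist.* Rejection in 12% to 15% of null trials requires doubled re-injury risk and half of the injured staying; the documents give neither. With no extra risk and half staying, rejection is about 4% to 8%.
- *Earlier injuries unbalance the groups, so the model must be stratified by them.* In-programme injury is an outcome the intervention is meant to change. In the null frailty model, the uninjured stratum alone gives a spurious hazard ratio of about 1.1 to 1.3 against POTs. Whether fewer earlier injuries belong to persistence is a choice of estimand, and covariates of a secondary model may be left to the analysis plan.

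**Conclusion.** The concern holds as an inconsistency with a consequence for one secondary analysis. The protocol gives two incompatible dates for the visit that anchors objective 4, and one of them admits in-programme falls as persistence events.

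Under the summary rule, with the plan's rates, no true later effect, equal risk across participants and no extra re-injury risk, the hazard ratio would be about 0.91 to 0.97 if half of the injured stay. It would be about 0.98 to 0.99 if one in ten stays. These figures illustrate size only: the share staying, the re-injury risk and the 1 to 6 further weeks are not in the protocol, and the sign may change if risk differs between people. Under the body sections this mechanism is absent.

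**What to change.** Reconcile the Schedule row of the Research Summary with Follow-up visits, End-of-study visit and Discontinuation criteria for a participant, so that the end-of-study visit has one date rule throughout.

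Separately, define the objective 4 window without reference to that visit. For every participant it starts on one common day, the day after the last session, and falls inside the programme window are not objective 4 events. Do not stratify by in-programme injury or report a separate uninjured stratum, for the reason given above.

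The common start removes programme time from the comparison but does not restore balance among those who remain. In the null frailty model with half of the injured staying it still gives 1.02 to 1.06, so the result should be read with that in mind.

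The cost is a short edit to the summary and to the objective 4 definition, plus a small loss of objective 4 events. No new data are needed, since the injury visit takes place on the day of the injury.

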### Biological parameters

A saliva sample will be collected during the initial evaluation visit, and the end-of-study visit (2 x 2 ml at each visit). These samples will be used to monitor markers of the corticotropic axis (cortisol and DHEA), and the autonomic nervous system (alpha-amylase and chromogranin).

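### Post-intervention posturography and saliva are not tied to completing the programme: injured or early-leaving participants may be measured on the day of injury or exit, and the two visit rules conflict

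*Protocol*

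**What the plan says.** **Timing.** The Schedule row of the Research Summary holds the end-of-study visit the day after the last session, "or on the day of the fall injury if it occurs before the end of the POT or active control intervention". On content it says: "This visit will include: paraclinical measurement of posture, self-report questionnaires (postural awareness and perceived stress) and saliva collection". The End-of-study visit section has the same measurements but a different early trigger: "the day they leave the course (for whatever reason), if this occurs before the end of the intervention". The discontinuation criteria for a participant also use leaving the course, not injury.

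**Injury visit.** Under Follow-up visits, a participant with a fall trauma "will attend an additional follow-up visit, which will take place on the day of the injury". That visit has posturography and both questionnaires, but no saliva.

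**Saliva.** Biological parameters gives two sampling times only: "A saliva sample will be collected during the initial evaluation visit, and the end-of-study visit".

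**Analysis.** Within the POTs group, objective 1 uses "posturography measurements pre- and post-intervention (paired samples comparison of means") and objective 2 uses "biological stress variables (paired samples comparison of means"). Postural awareness (PAS) and perceived stress (PSS) scores go into repeated measures ANOVA. Nothing in that section says whether an injury-day or exit-day record counts as post-intervention.

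**Missing data.** Statistical methods replaces missing values by the mean of the participant's group.

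**The concern.** Objectives 1 and 2 are meant to show how POTs might prevent falls: through better postural awareness and balance, and through a smaller stress response. Under the Research Summary rule, the fall injury itself fixes when these mechanism measures are taken. A balance recording or saliva sample from that day comes after only part of the programme, and may carry the acute effect of the trauma or of leaving the course. If it enters the paired test as an ordinary post value, the mean change mixes a training effect with something else, and neither a positive nor a null result can be read cleanly.

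The conflict between the two timing rules matters in its own right. For someone injured who stays on the course, one rule puts the end-of-study visit on the injury day and the other does not. Under the first, it falls on the same day as the additional visit, so posturography, PAS and PSS are scheduled twice. A post-programme saliva sample from that person would not be scheduled at all.

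**Working it through.** **1. The plan's own figure.** Inputs from the sample size section: 50% v 35%, two-sided 0.05, power 0.80, 10% drop-out.

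- n = [1.96 × √(2 × 0.425 × 0.575) + 0.8416 × √(0.25 + 0.2275)]² / 0.15² = 170 per group, or 183 with continuity correction.
- 183 / 0.90 = 204, close to the stated 200.
- After 10% drop-out, 200 × 0.90 = 180 per group. This is the number of pairs used below.

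**2. How many post values could be early.**

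- Research Summary rule, with the 35% rate applied to the three weeks: 0.35 × 200 = 70, or 0.35 × 180 = 63. On-schedule pairs: 180 − 63 = 117.
- End-of-study visit rule: an injured participant who stays has an ordinary visit, so the injury-day share is below 35%.
- The 35% has no stated time window. Objective 4 counts falls between the end of the study and the end of the selection course, so the course can outlast the three weeks. If the rate covers the whole course, the three-week share is again lower.
- Those leaving for other reasons add exit-day values under the End-of-study visit rule.

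The affected share is therefore uncertain and is varied here over 10%, 20% and 35%.

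**3. Illustrative effect on a paired test.** Assumptions not in the documents: pre/post correlation 0.5, early values shifted by s = 0.5 baseline SD, no true change. The SD of the change is √(2 × (1 − 0.5)) = 1 baseline SD. With affected share f:

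- mean bias = f × s
- SD = √(1 + f(1 − f)s²)
- λ = (bias / SD) × √180
- rejection = Φ(λ − 1.96) + Φ(−λ − 1.96)

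| f | bias | SD | λ | rejection |
|---|---|---|---|---|
| 10% | 0.050 | 1.011 | 0.66 | 0.10 |
| 20% | 0.100 | 1.020 | 1.32 | 0.26 |
| 35% | 0.175 | 1.028 | 2.28 | 0.63 |

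A true benefit of 0.209 SD has 80% power without the shift. If the shift opposes it, the chance of detecting it falls to 0.56, 0.30 and 0.06 at the three shares.

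**4. What restricting to on-schedule pairs does.** It conditions on being uninjured. The Protocol hypothesises that poor postural control raises fall risk, so this subset is selected.

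- In simulations with no true change and injury odds rising 1.28, 1.65 or 2.2-fold per SD of worse balance, uninjured-only pairs rejected in 7%, 15% and 29% of trials, as apparent improvement.
- That direction assumes injury tracks balance late in the course. If it tracks baseline balance, regression to the mean gives apparent worsening instead.

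**5. What group-mean replacement would do.** Suppose 63 excluded post values were filled with the mean of the other 117, with no selection at all.

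- True variance of the mean change: 1/117 + 1/180 − 2 × 0.5/180 = 1/117.
- The paired test would use about 1/180.
- The standard error is too small by √(180/117) = 1.24, so the effective critical value is 1.96/1.24 = 1.58 and rejection is about 11%.

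**6. Questionnaires.** PAS and PSS are also collected before sessions, so only the last value in the series is an injury-day or exit-day value.

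**The case against.** The strongest reply is that the analysis section never says injury-day or exit-day values are pooled as post-intervention. Biological sample collection codes additional visits separately from the final visit, and choosing records for a secondary test is commonly left to a statistical analysis plan. That is fair as far as it goes. But for an injured participant under the Research Summary rule, or a leaver under the End-of-study visit rule, the early visit is the end-of-study visit, and its saliva sample is the only later one. An analysis plan could exclude that value but could not supply one never collected, and the conflict in timing sits in the Protocol.

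A reader might go further and infer any of the following, none of which the documents support:

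- **A third of the POTs group is certainly affected.** This needs the Research Summary rule and a three-week reading of the 35% rate.
- **The tests measure the injury itself and are biased against POTs.** No size or direction is given. An early value mixes partial training, the acute event and the person's prior balance. The description of trauma as typically of the lower limbs comes from one marine commando course.
- **The difference in injury rates biases a comparison with control.** Objectives 1 and 2 are planned within the POTs group only.
- **Keeping only on-schedule pairs cures the problem.** Steps 4 and 5 show that this selects on the primary outcome, and that group-mean replacement would add a further error.

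**Conclusion.** The point holds as a should-fix. The two timing rules contradict each other, and the plan does not tie the post value of posturography and saliva to completion of the six sessions. Up to 35% of the POTs group could have an injury-day post value, and the true share may be well below that. Under an assumed shift of 0.5 SD, correlation 0.5 and 180 pairs, false rejection runs from about 10% to 63% over shares of 10% to 35%. These figures show sensitivity and are not an estimate of the actual bias. PAS and PSS are touched only at the last time point. The primary Cox analysis of fall injuries is unaffected.

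**What to change.** 1. Reconcile the Research Summary, Follow-up visits and End-of-study visit sections on when the end-of-study visit falls, and on which visit an injured participant who stays on the course attends.
2. In the analysis of secondary objectives, define the post-intervention value as the one taken the day after the last session. Report injury-day and exit-day values as a separate time point.
3. Label the paired posturography and saliva results as applying to on-schedule participants (about 117 of 180 at a 35% share), a subset selected on the primary outcome. Show the analysis of all values beside them as a sensitivity analysis.
4. For PAS and PSS, use a likelihood-based mixed model on the session measurements up to injury or exit.
5. State that group-mean replacement does not fill the excluded post values.

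**Cost.** Wording and analysis only. The price is fewer pairs and a selected subset, which must be stated with the result.
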